### Monitoring arrangements

The trial will be monitored on site in accordance with the trial monitoring plan. This will be an on-going activity from the time of initiation until trial close-out and will comply with the principles of Good Clinical Practice (GCP) and applicable regulatory requirements. The Data Monitoring and Ethics Committee (DMEC) will safeguard the rights, safety and wellbeing of trial participants, monitor data and make recommendations to the Trial Steering Committee (TSC) on whether there are ethical or safety reasons why the trial should not continue. They will monitor the overall conduct of the study to ensure the validity and integrity of the study findings, and will meet annually. The DMEC will comprise independent members with at least one statistician and two respiratory specialists. A DMEC charter will detail the terms of reference of the DMEC, including membership and roles and responsibilities.

### Adverse events

All adverse events (AEs) that are directly observed and spontaneously reported by the patient will be recorded on their CRF. Signs and symptoms of pulmonary exacerbations collected as outcomes of the trial will not be reported as AEs. Therefore, if a patient requires hospitalisation or prolongation of existing hospitalisation as a result of an exacerbation, this will not be reported as a serious adverse event (SAE). The Principal Investigator or designee will assess severity, seriousness, causality, severity and expectedness for each AE and these will be reported in keeping with regulatory requirements.

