### Objectives

The primary objective of the CLEAR trial is to determine whether HTS (6%) and/or carbocisteine reduces the mean number of exacerbations over 52 weeks. Secondary objectives are to determine whether HTS and/or carbocisteine improve disease-specific HRQoL, reduce time to next exacerbation, reduce number of days of antibiotics for treatment of exacerbations, improve generic HRQoL, are acceptable from a patient satisfaction perspective, are associated with adverse events (AEs) and improve lung function over 52 weeks. The study will also assess cost effectiveness and treatment adherence.

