### Treatment discontinuation

All patients allocated to a treatment group including HTS 6% will complete a drug response assessment prior to commencing HTS in accordance with a study-specific guideline and if they do not pass this they will not continue on the study. Participants may withdraw from treatment at any time, without providing an explanation, or if discontinuation is considered by the medical team to be in the best interests of the patient. Anticipated reasons for withdrawal include intercurrent significant illness, occurrence of intolerable side effects, patient request, protocol violations or decision that the study drug should be discontinued on safety grounds. A participant may be withdrawn from the study at the discretion of the Investigator due to safety concerns.

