#### Treatment Satisfaction Questionnaire for Medication

At each study visit, participants (except those randomised to the standard care group) will be asked what they think about the effectiveness, side effects and convenience experienced when using the medication over the last 2–3 weeks, or since they last used it. Patients assigned to the group combining HTS and carbocisteine (intervention group 3) will be asked to complete separate questionnaires for each treatment.

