### Randomisation and blinding

Treatment allocation at each site will be assigned using a concealed automated randomisation process provided by an external organisation. Participants who give their consent will be allocated using a fixed block size to one of the four groups (three intervention groups or one standard care group) in a 1:1:1:1 ratio using a central randomisation system. Randomisation will be stratified by (1) site, (2) exacerbations in the last year (2–3 times, > 3 times) (to minimise baseline imbalances in antibiotic use) and (3) current use of macrolides (yes, no). The trial is open label, and patients, investigators and outcome assessors will be aware of treatment allocation.

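### Adverse events are recorded passively while the drug groups, but not standard care, are asked about side effects at each visit, so the adverse event comparison is open to ascertainment bias

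*Protocol article*

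**What the plan says.** The Adverse events section gives the recording rule: "All adverse events (AEs) that are directly observed and spontaneously reported by the patient will be recorded on their CRF". It names two routes, observation by staff and unprompted report by the patient.

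The Treatment Satisfaction Questionnaire section sets out an activity that differs by group and is repeated at every visit. Its wording is: "participants (except those randomised to the standard care group) will be asked what they think about the effectiveness, side effects and convenience experienced". Patients in the combination group "will be asked to complete separate questionnaires for each treatment".

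The Randomisation and blinding section states that "The trial is open label, and patients, investigators and outcome assessors will be aware of treatment allocation". Under Objectives, the secondary aims include whether the drugs "are acceptable from a patient satisfaction perspective, are associated with adverse events (AEs) and improve lung function over 52 weeks", and the Outcomes section lists adverse events among the secondary outcomes over 52 weeks.

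Three further statements bear on the point:

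- The RSSQ section has a team member administer a symptom questionnaire at each study visit, with no restriction by group.
- The Statistical analysis section says safety data will be summarised descriptively.
- The Treatment discontinuation section says "All patients allocated to a treatment group including HTS 6% will complete a drug response assessment prior to commencing HTS".

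**The concern.** When events are recorded mainly because patients volunteer them, the count depends on how often patients are led to think about them. Here the number of side-effect questionnaires per visit rises with the number of allocated drugs: none in standard care, one in each single-drug group, two in the combination group. A patient who has just answered questions on side effects is more likely to mention one to staff, and those staff know the allocation.

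At stake is a stated secondary objective. If non-serious events are captured more fully in the drug groups, the tables will show an excess over standard care even where the true rates are equal. Analysis cannot repair this afterwards, because nothing collected would show what standard care patients would have reported if asked. Serious events are less exposed, since they usually come to notice without prompting.

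**Working it through.** The article gives no adverse event rate, capture rate or power figure, so there is no stated number to reproduce. The check has two parts.

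**1. What prompts each group, as stated in the article**

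| Source of prompting or observation | Standard care | Carbocisteine | HTS | Combination |
|---|---|---|---|---|
| Satisfaction questionnaires per visit, covering side effects | 0 | 1 | 1 | 2 |
| RSSQ at each visit (no arm restriction stated) | yes | yes | yes | yes |
| Drug response assessment before HTS | no | no | yes | yes |

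The RSSQ covers cough and sputum, blood in the sputum, breathlessness, tiredness, sinus symptoms, appetite and fever. It therefore prompts all groups alike for respiratory and some systemic symptoms. It is not a general enquiry about side effects: gastrointestinal and skin effects, for example, are not among its listed items. The imbalance that remains comes mainly from the first row and concerns symptoms outside the RSSQ's content.

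**2. What unequal capture would do (illustration only)**

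Assume the same true event probability p in every group, capture fraction s in standard care, and capture fraction q in every drug group. No extra effect is given to the second questionnaire in the combination group.

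- One drug group against standard care: recorded ratio = pq / ps = q/s.
- Factorial margin, for example both HTS groups against the other two: all HTS patients have capture q. Half of the comparator takes carbocisteine (q) and half is standard care (s). The ratio is q / [(q + s)/2] = 2q/(q + s).

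In both cases p cancels.

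| s (assumed) | q (assumed) | Drug group v standard care, q/s | Factorial margin, 2q/(q + s) |
|---|---|---|---|
| 0.50 | 0.50 | 1.00 | 1.00 |
| 0.50 | 0.65 | 0.65/0.50 = 1.30 | 0.65/0.575 = 1.13 |
| 0.50 | 0.80 | 0.80/0.50 = 1.60 | 0.80/0.65 = 1.23 |
| 0.60 | 0.70 | 0.70/0.60 = 1.17 | 0.70/0.65 = 1.08 |
| 0.60 | 0.90 | 0.90/0.60 = 1.50 | 0.90/0.75 = 1.20 |
| 0.80 | 0.90 | 0.90/0.80 = 1.13 | 0.90/0.85 = 1.06 |

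In absolute terms, take p = 0.3 (assumed) and the 95 patients per group from the Sample size section. With s = 0.60 and q = 0.90, the recorded proportions are 0.3 × 0.60 = 18% and 0.3 × 0.90 = 27%, or about 17 against 26 patients with no true difference. With q = 0.70 they are 18% and 21%.

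The ratio returns to 1.00 whenever q = s, however low the common capture. Equal questioning therefore matters more here than complete questioning.

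**The case against.** The strongest reply is that the link from questionnaire to adverse event record is nowhere stated. Read literally, an answer on a satisfaction form is neither observed by staff nor volunteered, so the recording rule may already keep it out. This stands in part: it rules out saying that the comparison is biased. It does not remove the indirect route, in which the form prompts a patient to mention something that then counts as volunteered.

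Second, standard care patients are not left unquestioned. The RSSQ, the quality-of-life instruments and the health service use questionnaire carry no stated arm restriction. This stands as a reduction of the imbalance, not its removal.

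Third, safety data are to be described, and no test of adverse events is planned. This stands, and it is why no false-positive rate is claimed here. A descriptive table can still mislead.

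Fourth, this is a condensed article, and the full protocol or case report form may hold a common adverse event question. It may, and its absence from the article is not the point. The article does state a recording rule and does state a group-specific questionnaire; the point rests on those two statements.

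Fifth, a medication satisfaction form cannot sensibly be given to patients without trial medication. Agreed. The remedy lies in adverse event recording, not in that form.

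A reader might also take events at the HTS drug response assessment to be an artefact of extra observation that should be set aside. The documents do not support this. Reactions at that assessment would be effects of HTS, and excluding them would favour it. Of patients who fail it, the article says "if they do not pass this they will not continue on the study". That takes HTS-intolerant patients out of later follow-up and works against an apparent HTS excess.

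**Conclusion.** The point holds as a risk of ascertainment bias, not as a demonstrated bias. The stated rule is passive, repeated side-effect questioning is confined to the drug groups, the trial is open label, and adverse events are a secondary objective and outcome. The likely direction is more recorded non-serious events in the drug groups than in standard care. For HTS the direction is less certain, because patients who fail the response assessment leave the study.

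The size cannot be derived from the article. The ratios of 1.3–1.6 against standard care, and 1.13–1.23 in the factorial margins, follow only from assumed capture of 50% against 65–80%. The distortion is zero if capture is equal. It is greatest where a drug group is set beside standard care and is diluted in the factorial main effects.

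A reader might infer that observation and spontaneous report are the only permitted sources of adverse events, or that standard care patients are never asked about symptoms. The text says neither: it does not exclude other sources, and the RSSQ section indicates symptom questioning with no stated restriction by group.

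**What to change.** - At each study visit, ask all four groups the same open, non-leading adverse event question, before the satisfaction questionnaire is given.
- State that satisfaction answers are kept separate from adverse event recording in the between-group comparison, except that any serious event is always recorded.
- Keep events at the HTS drug response assessment in the comparison. Flag them by timing and also tabulate them separately, so that readers can see how much of any HTS excess arises there.

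The cost is one scripted question per visit on the existing case report form and a short protocol addition, with no new visits. More adverse event entries should be expected overall, including in standard care, with the data entry that goes with them. If the full protocol already has such a question for all groups, only the separation of satisfaction answers and the timing flag would need to be added.

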### End of study

The main trial analysis will be conducted at 52 weeks; however, the formal end of the study will be at the end of the 104-week follow up to establish mucoactive drug use in participants. The trial will be stopped prematurely if mandated by the responsible Research Ethics Committee (REC), Medicine and Healthcare Products Regulatory Agency (MHRA), Sponsor (e.g. following advice from the TSC based on recommendations from the DMEC) or if funding for the trial ceases. The REC that originally gave a favourable opinion of the trial and the MHRA who issued the Clinical Trial Authorisation (CTA) will be notified in writing once the CLEAR trial has been concluded or if it is terminated early.

### Site training

All sites will undertake comprehensive site initiation visits (SIV). PARI or the research team will provide training to sites on the eFlow nebuliser system with eTrack controller, SpiroSense*Pro* and *my*SpiroSense spirometer. Follow-up refresher training will be delivered prior to the first patient’s first visit, and sites will be advised to send questions to the research team at any time. A document containing frequently asked questions will be maintained and circulated to sites, along with a regular newsletter detailing any updates and news on the trial, such as recruitment milestones.

### Trial management arrangements

Trial-specific oversight committees will be convened for the CLEAR trial. These will include a Trial Management Group (TMG), TSC and DMEC. The NICTU will facilitate the setting up and the co-ordination of these committees. All study amendments will be managed by the NICTU and communicated appropriately.

### Patient and public involvement

Service users are involved in the CLEAR trial in both a consultative and collaborative capacity and have influenced this protocol, including the choice of interventions and outcomes to measure. The Chair of Primary Ciliary Dyskinesia Family Support Group UK and a BE carer is a co-applicant on the trial grant and a member of the TSC. The study is registered with the INVOLVE open-access database, which registers research healthcare projects involving members of the public as partners in the research process.

### Data sharing and data access

Requests for data sharing will be reviewed on an individual basis by the Chief Investigator (CI) and TMG. Following the publication of the trial’s main outcomes, there may be scope to conduct additional analyses on the data collected. In such instances, formal requests for data will be made to the CI for discussion with the TMG. If publications might arise from such analyses, those responsible will provide the CI with a copy of the intended manuscript for approval prior to submission to a journal.

## Discussion

CLEAR is a pragmatic effectiveness trial. It was designed as an open-label trial (in preference to a blinded trial) because of factors including the prohibitive cost and feasibility of conducting a trial with blinded patients, practitioners and/or outcome assessors. There is increasing support for trials to use more pragmatic research designs [37], especially in therapy trials where blinding is not feasible [38] or practical and when the funding required to implement blinded trials could be better used to optimise rigour in other areas of trial delivery (Anand R, Norrie J, Bradley JM, McAuley DF, Clarke M: Fool’s gold? Why double blind trials are not always best, submitted). The CLEAR trial also has added value through the embedding of low-cost sub-studies to resolve important uncertainties about trial methods [27].

The findings of the CLEAR trial will be published in a peer-reviewed journal and will help inform national and international guidelines on the use of HTS and carbocisteine as mucoactive drugs for treatment of BE. A lay person’s summary will be sent to local and national patient support and liaison groups, including the European Lung Foundation BE Patient Advisory Group and the British Lung Foundation as well as similar organisations in devolved nations of the UK. A report of the study findings will be provided for the INVOLVE registry. Following journal publication, key findings will be posted on institutional websites that are freely available to the general public and others.

In summary, HTS and carbocisteine are the two most commonly used mucoactive agents in BE, being prescribed to up to 20% of patients but without a solid evidence-base for their effectiveness. The CLEAR trial will demonstrate whether these one-in-five patients with BE are being asked to take burdensome medications that are ineffective or, if effective, whether more consideration needs to be given to prescribing these medications to the remaining 80% of patients with BE.

## Trial status

Recruitment to the CLEAR trial started in July 2018 and at the time of proof reading of this manuscript (December 2019), 130 patients had been recruited, with recruitment aimed to be completed by August 2020. Analysis will begin after recruitment and follow up are completed and the database has been cleaned and locked. The current protocol version is 3.0 (14/05/2018).

## Data Availability

Not applicable.

## Abbreviations

AE: Adverse event
ANCOVA: Analysis of covariance
ANOVA: Analysis of variance
AR: Adverse reaction
BE: Bronchiectasis
BHSCT: Belfast Health and Social Care Trust
BRONCH-UK: UK Bronchiectasis Registry
BTS: British Thoracic Society
CF: Cystic fibrosis
CI: Chief Investigator
CRF: Case report form
CRN: Clinical Research Network
CTA: Clinical Trial Authorisation
CTU: Clinical Trials Unit
DMEC: Data Monitoring and Ethics Committee
DMP: Data management plan
EMBARC: European Multicentre Bronchiectasis Audit and Research Collaboration
EQ-5D-5 L: EuroQoL five dimension five level questionnaire
EudraCT: European Clinical Trials Database
FEF: Forced expiratory flow
FEV_1_: Forced expiratory volume in one second
FVC: Forced vital capacity
GCP: Good Clinical Practice
HRCT: High-resolution computed tomography
HRQoL: Health-related quality of life
HTA: Health and Technology Assessment Programme
HTS: Hypertonic saline
IB: Investigator brochure
ICH: International Conference of Harmonisation
IMP: Investigational medicinal product
IRB: Institutional Review Board
ISRCTN: International Standard Randomised Controlled Trial Number Register
MACRO: Clinical Trials Database
MHRA: Medicine and Healthcare Products Regulatory Agency
NHS: National Health Service
NICTU: Northern Ireland Clinical Trials Unit
NIHR: National Institute for Health Research
NMB: Net monetary benefit
PI: Principal Investigator
PICO: Population, intervention, comparison and outcome(s)
PPI: Patient and public involvement
QALY: Quality-adjusted life year
QoL-B: Quality of Life - Bronchiectasis
REC: Research Ethics Committee
RSI: Reference safety information
RSSQ: Respiratory and Systemic Symptoms Questionnaire
SAE: Serious adverse event
SAP: Statistical analysis plan
SAR: Serious adverse reaction
SGRQ: Saint George’s Respiratory Questionnaire
SOPs: Standard operating procedures
SPC: Summary of product characteristics
SUSAR: Suspected unexpected serious adverse reaction
SWAT: Study within a trial
TMG: Trial Management Group
TSC: Trial Steering Committee
WTP: Willingness to pay
